## **2. OBJECTIVES**

### **2.1 Primary objective**

Decay rate of the SARS-CoV-2 viral load logarithmic curve obtained via nasopharyngeal swab between the baseline and the fifth and tenth days after randomization.

## 2.2 Secondary objective

Evaluate the effect of halofuginone on:

- I. Hospital admission between randomization and the day 28;
- II. Need for invasive mechanical ventilation between randomization and day 28;
- III. Time to resolve symptoms until the tenth day;
- IV. Ordinal clinical scale of symptoms on 14th (1. not hospitalized, without limitation of daily activities; 2. not hospitalized, with limitation of daily activities; 3. hospitalized, without the need for supplemental oxygen; 4. hospitalized, requiring supplemental oxygen; 5 hospitalized, requiring high-flow nasal oxygen therapy, non-invasive mechanical ventilation, or both; 6. hospitalized, requiring blood oxygenation through a membrane system, invasive mechanical ventilation, or both; 7. Death).

## 3. METHODS: RESEARCH SUBJECTS, INTERVENTIONS AND OUTCOMES

### 3.1 Study design

Multicenter clinical trial, phase 2, randomized, double-blind, placebo-controlled in 150 patients.

### 3.2 Study locations

The study will be conducted in 2-5 Brazilian hospitals.

### 3.3 Recruitment plan

Patients will be recruited from outpatient clinics and emergency rooms at participating institutions.

### 3.4 Eligibility Criteria

#### 3.4.1 Inclusion Criteria

1. Adult patients (age  $\geq$  18 years);
2. COVID-19 diagnosis confirmed by:
  - a. Detection of SARS-CoV-2 by RT-PCR, or
  - b. Rapid genetic or antigen tests registered by ANVISA;
3. Mild or moderate symptoms without indication for hospitalization;
4. Symptoms started seven days ago or less;
5. Be able to access the study's online questionnaire.

#### 3.4.2 Exclusion Criteria

1. Pregnant or lactating women;
2. Known allergy or hypersensitivity to the study drug;
3. Patients at high risk of bleeding, defined by:
  - a. Previous Intracranial hemorrhage,
  - b. Ischemic stroke in the last 3 months,
  - c. Anatomical vascular alteration of the central nervous system known, such as aneurysms or arteriovenous malformations,
  - d. Malignant neoplasm of the central nervous system known,
  - e. Metastatic solid neoplasia,
  - f. Significant closed head or facial trauma in the last 3 months (defined as any trauma that required medical evaluation or hospitalization),
  - g. Known intracranial abnormalities not listed as absolute contraindications (e.g., benign intracranial tumor),
  - h. Bleeding in the last 2 to 4 weeks (excluding menstrual bleeding),

- i. Surgical procedure in the last 3 weeks,
  - j. Current use of full-dose anticoagulants (warfarin, enoxaparin or new anticoagulants) or dual antiplatelet therapy,
  - k. Thrombocytopenia ( $<100,000/\text{mL}$ ) or INR (international standardized ratio)  $> 1.3$ ;
4. Renal failure, defined as glomerular filtration rate (GFR) estimated by the formulas MDRD or CKD-EPI  $<30\text{mL}/\text{min}/1.73\text{m}^2$ ;
  5. Previous participation in the study;
  6. History of liver disease (cirrhosis) reported by the patient or in medical records, presence of esophageal varices or presence of ascites;
  7. Decompensated heart failure, defined by the presence of dyspnea attributed to cardiac cause, edema of the lower limbs, crackles on pulmonary auscultation or pathological jugular turgency.
  8. Participation in other clinical trials with antivirals in COVID-19

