### 3.6 Procedures for verifying the eligibility criteria

After signing the Informed Consent, it will be collected serum creatinine, prothrombin time, platelet count (blood count) and rapid pregnancy tests (in the case of women of childbearing age) to confirm the eligibility criteria. If the patient has underwent part or all the tests in the last 3 days, the results may be considered to verify the eligibility.

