#### *3.10.2 Additional study interventions*

Knowing that the most commonly reported adverse events with the use of halofuginone in phase I trials were nausea and vomiting after taking the medication, patients who present such symptoms will be advised to prophylactic use of an antiemetic (ondansetron 4mg orally) between 30 minutes and 1h taking the study medication. This use should be maintained as long as the patient is using the study medication. If the patient does not experience nausea or vomiting with the use of the study medication, he should not use the antiemetic. Ondansetron will be provided by the study free of charge to patients who are not allergic to it. In case of allergy to ondansetron, metoclopramide 10mg will be offered as an antiemetic alternative.

In addition, there will be no other mandatory intervention in the clinical study. Patients will receive standard treatment indicated by the care team, as well as specific

guidelines on the disease. Specific treatment for COVID-19 may include, but is not limited to:

- Antibiotic therapy for secondary infection;
- Medications to treat symptoms such as fever, pain and nausea;
- Antivirals if indicated by the patient's medical team;
- Other interventions, if indicated by the patient's medical team.

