### *3.10.3 Treatment interruption*

Treatment should be stopped in the following situations:

- Patient presents hospitalization; **OR**
- Patient who had validated antigen test result and later presented a negative RT-PCR result performed on first day of the participation; **OR**
- Patient who has clinical indication for use of full-dose anticoagulants; **OR**
- Presence of serious adverse events.

In the situation of treatment interruption due to negative RT-PCR test for SARS-CoV-2, no additional clinical and laboratory data will be collected.

In other situations, the patient will be instructed to stop using the study medication and there will be no additional collection of laboratory tests. Clinical data collection via online questionnaire and clinical follow-up via phone call will be maintained.

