**Table 1.** Toxicity in the first two-week cycle according to the common terminology of adverse events of the National Cancer Institute version 2.018 a

| Dose
mg/day | No. of
patients | Leukopenia |   |   |   | Neutropenia |   |   |   | Thrombocytopenia |   |   |   | Nausea |   |   |   | Vomiting |   |   |   | Fatigue |   |   |   | DLT |
|----------------|--------------------|------------|---|---|---|-------------|---|---|---|------------------|---|---|---|--------|---|---|---|----------|---|---|---|---------|---|---|---|-----|
|                |                    | 1          | 2 | 3 | 4 | 1           | 2 | 3 | 4 | 1                | 2 | 3 | 4 | 1      | 2 | 3 | 4 | 1        | 2 | 3 | 4 | 1       | 2 | 3 | 4 |     |
| 1              | 4                  |            |   |   |   |             |   |   |   | 1                |   |   |   | 3      |   |   |   | 2        |   |   |   | 3       |   |   |   | 1*  |
| 2              | 6                  |            |   |   |   |             |   |   |   |                  |   |   |   | 1      | 4 |   |   | 2        | 3 |   |   | 2       | 3 |   |   |     |
| 3.5            | 3                  |            |   |   |   |             |   |   |   |                  |   |   |   |        | 1 | 1 |   | 1        | 1 |   |   |         |   | 2 |   | 2   |
| 0.5            | 5                  | 1          |   |   |   |             |   |   |   |                  |   |   |   | 1      |   |   |   | 2        |   |   |   | 1       |   |   |   |     |
| 0.5 2x         | 7                  |            |   |   |   |             |   |   |   |                  |   |   |   | 2      |   |   |   | 1        | 1 |   |   | 3       |   |   |   | 2*  |

a Adapted from de Jong et al.  
b Abbreviations: DLT, dose-limiting toxicity.  
\* DLT for chronic administration

Seven of the 24 patients in the study experienced bleeding during treatment with halofuginone. In preclinical studies, halofuginone inhibited the migration of endothelial cells and prevented their organization in networks similar to capillary anastomoses. *In vivo* studies, no thromboembolic events or bleeding were observed. Table 2 describes the bleeding episodes and doses for each patient.

**Table 2.** Bleeding episodes a

| Patient | Cycle b | Dose         | Description                                                                                                    |

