#### Research participants' data collected at Day 1 - baseline (Table 4)

- Demographic data: age, gender
- Baseline data: comorbidities, previous and current use of medications, date of onset of symptoms, clinical symptoms, date of positive SARS-CoV-2 test if available, clinical signs (temperature, heart rate, systolic and diastolic blood pressure, respiratory rate, peripheral oxygen saturation).

**Table 4.** Data from research participants and timeline

|                       | Baseline/
D1 | D2 | D3 | D4 | D5 | D6 | D7 | D8 | D9 | D10 | D14 | D28 |
|-----------------------|-----------------|----|----|----|----|----|----|----|----|-----|-----|-----|
| Screening             | X               |    |    |    |    |    |    |    |    |     |     |     |
| Eligibility           | X               |    |    |    |    |    |    |    |    |     |     |     |
| Informed Consent Form | X               |    |    |    |    |    |    |    |    |     |     |     |
| Randomization         | X               |    |    |    |    |    |    |    |    |     |     |     |
| Interventions         |                 |    |    |    |    |    |    |    |    |     |     |     |

|                                                       |   |   |   |   |    |   |   |   |   |   |   |   |
|-------------------------------------------------------|---|---|---|---|----|---|---|---|---|---|---|---|
| Halofuginone 1mg/day                                  | X | X | X | X | X  | X | X | X | X | X |   |   |
| Halofuginone 0.5mg/day                                | X | X | X | X | X  | X | X | X | X | X |   |   |
| Placebo                                               | X | X | X | X | X  | X | X | X | X | X |   |   |
| Data collection and tests                      |   |   |   |   |    |   |   |   |   |   |   |   |
| Demographic Data                                      | X |   |   |   |    |   |   |   |   |   |   |   |
| Baseline Data                                         | X |   |   |   |    |   |   |   |   |   |   |   |
| Symptoms and signs                                    | X | X | X | X | X  | X | X | X | X | X |   |   |
| RT-PCR SARS-CoV-2                                     | X |   |   |   | X  |   |   |   |   | X |   |   |
| Laboratory tests                                      | X |   |   |   | X* |   |   |   |   | X |   |   |
| Safety Data
(via patients online
questionnaire) | X | X | X | X | X  | X | X | X | X | X |   |   |

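### Exclusion 8 bars only other antiviral trials and only at entry, leaving room for co-enrolment in a masked trial of full-dose anticoagulation or dual antiplatelet therapy, where exclusion 3j cannot be verified

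*Protocol*

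**What the plan says.** Protocol 3.4.2, exclusion 8, reads "Participation in other clinical trials with antivirals in COVID-19", and the synopsis has the same wording. Exclusion 5 covers only earlier participation in this study. No other section limits participation in other trials.

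Bleeding is the risk around which eligibility is built. Section 3.10.4 reports of the cited phase I study: "Seven of the 24 patients in the study experienced bleeding during treatment with halofuginone". Section 8.4 relies on the exclusion criteria to mitigate that risk. Two rules depend on knowing a patient's antithrombotic treatment:

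- Exclusion 3j, at entry: "Current use of full-dose anticoagulants (warfarin, enoxaparin or new anticoagulants) or dual antiplatelet therapy".
- The stop rule in 3.10.3, during treatment: "Patient who has clinical indication for use of full-dose anticoagulants".

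Concomitant care is open. Section 3.10.2 allows "Antivirals if indicated by the patient's medical team" and "Other interventions, if indicated by the patient's medical team". The laboratory checks for eligibility in 3.6 are "serum creatinine, prothrombin time, platelet count (blood count") and a pregnancy test. The baseline data in 3.11.5 include "comorbidities, previous and current use of medications", but not participation in other trials.

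**The concern.** Exclusion 8 anticipates that these patients may be approached for other COVID-19 trials, but it deals with one drug class. Exclusion 3j and the anticoagulant stop rule assume that the site knows what the patient takes. In a masked trial of full-dose anticoagulation or dual antiplatelet therapy, neither the patient nor the site knows.

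Two things are at stake. A patient could receive the combination that the protocol sets out to avoid without any protocol rule being visibly broken. And bleeding, a named safety outcome in 4.3, could occur on two masked products with no means of saying which one contributed.

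**Working it through.** No power, rate or sample-size figure is in dispute, so the check is a reading of the rules against one another.

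**Step 1. Which other trials escape exclusion 8 and also engage a bleeding rule?**

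| Other trial | Barred by exclusion 8? | Exclusion 3j | Anticoagulant stop rule (3.10.3) |
|---|---|---|---|
| Masked full-dose anticoagulant | No | Relevant, not verifiable | Would not clearly trigger |
| Masked dual antiplatelet | No | Relevant, not verifiable | Not covered |
| Open-label full-dose anticoagulant or dual antiplatelet | No | Identifies the patient at entry | Outside this point: the treatment is known |
| Single antiplatelet or lower-dose anticoagulant | No | Not covered | Not covered |
| Antibody or immunomodulator | No (a neutralising antibody might be read as an antiviral) | Not covered | Not covered |

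Only the first two rows carry the concern.

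**Step 2. Why the stop rule is uncertain.** It is triggered when the patient's clinical condition calls for full-dose anticoagulation. Random assignment in another trial is not clearly such an indication, and under masking the site does not know whether an anticoagulant was assigned.

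**Step 3. Would other procedures expose the second product?**

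- *At entry.* Prothrombin time is measured and an INR above 1.3 excludes (3k). That would catch some anticoagulant exposure but not all, and neither it nor a platelet count identifies antiplatelet treatment. Section 3.6 also accepts results up to 3 days old.
- *During treatment.* The next planned coagulation tests are on Day 10 (3.8.3), the last day of dosing. The daily questionnaire (3.11.5) asks about symptoms, signs and use of study medication.
- *After treatment.* The contents listed for the Day 14 and Day 28 calls (3.8.4) do not include other trials.
- *After an event.* The emergency code break (3.10.6) opens this trial's code only. The causality categories in 8.6.2 ask whether concomitant therapy explains the event, which cannot be judged while that therapy is masked.

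**Step 4. How finely can the safety data resolve a bleed?**

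- Phase I background: 7 / 24 = 29% of patients bled.
- One bleed in an arm of 50: 1 / 50 = 2 percentage points.
- One bleed at the interim look at 60 patients, assuming equal arms of 60 / 3 = 20: 1 / 20 = 5 percentage points.

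The last two figures hold for a bleed from any cause. They show that attribution of single events matters in a trial of this size. They say nothing about how often co-enrolment would happen.

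**The case against.** The best case on the other side has five parts.

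**Scope is a choice.** Exclusion 8 is consistent between synopsis and body, and barring only trials of the same class is a legitimate decision. This stands: nothing is misstated. The scope matters only because it leaves another stated rule unverifiable in one situation.

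**Most safeguards still work.** A reader might infer that the bleeding protections as a whole fail under co-enrolment. The protocol does not support that. Items 3a to 3i and 3k are unaffected, serious adverse events and hospitalisation still stop study drug, and a site that learns of the other trial could decline the patient on possible current use. The last safeguard depends on the site's judgement, and only at entry.

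**Many trial types are irrelevant.** A reader might extend the point to antibody, immunomodulator or single-antiplatelet trials. Neither 3j nor the anticoagulant stop rule mentions these, so no bleeding rule is defeated. An antibody trial might affect viral load, but 3.10.2 already permits clinician-indicated antivirals and other interventions, so widening exclusion 8 would not close that route.

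**No bias between arms is implied.** A reader might conclude that co-enrolment distorts the comparison systematically. Allocation is randomised, concealed and blinded (3.9), so co-enrolment is not expected to differ by arm. What remains is unexplained variation in sparse events, possible interaction, and risk to the individual.

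**The scenario may not occur.** Participants are outpatients with no indication for admission, and study drug stops on hospitalisation, so an inpatient anticoagulation trial would not overlap with dosing. Nothing in the protocol shows that masked full-dose trials recruit from the same clinics. This stands too, and it is why no count of affected patients is offered.

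**Conclusion.** The narrow point holds. As written, the protocol permits co-enrolment in a masked trial of full-dose anticoagulants or dual antiplatelet therapy. There, 3j cannot be verified, the anticoagulant stop rule would not clearly trigger, and a bleed could not be attributed to one product or the other. The gap is present at entry and wider afterwards, because exclusion 8 is not carried past randomisation and other-trial participation is not among the data listed for collection.

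The size is unknown. The number affected depends on a co-enrolment rate that the protocol does not give, and it may be zero. The conclusion rests on two assumptions: that such a masked trial could recruit these patients, and that it would accept someone already on an investigational product. The point is an inexpensive improvement to a stated safeguard. It is not a flaw that threatens the primary analysis.

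**What to change.** - Reword exclusion 8 in 3.4.2 and the synopsis to cover participation in any other interventional trial of a drug or biological product, and state that it applies at entry and through follow-up to Day 28.
- Record other-trial participation at baseline, in the existing daily questionnaire to Day 10, and at the Day 14 and Day 28 calls. The daily questionnaire is the part that matters for exposure, because the calls come after the last dose. The calls serve attribution of later events.
- Reconcile exclusion 8 with 3j and 3.10.3, so that the protocol says what follows if a participant co-enrols after randomisation. What that consequence should be is for the sponsor and investigators to decide.

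Routine care under 3.10.2 need not change. The cost is a short amendment, one question added to forms and contacts already planned, and a small loss of recruitment among patients in other drug trials.

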### 3.5 Procedures for COVID-19 diagnosis

For inclusion in the study, patients must present a diagnosis of SARS-CoV-2 infection defined by a positive RT-PCR test performed by the study center itself or present a confirmatory examination by RT-PCR performed at another center. If the time the result is available at the center takes more than 24 hours and the patient has carried out rapid automated tests or commercially similar, or rapid Antigen, although they are diagnostic tools registered by ANVISA to confirm the presence of SARS-CoV2, these results will be accepted for inclusion in the study.

### 3.6 Procedures for verifying the eligibility criteria

After signing the Informed Consent, it will be collected serum creatinine, prothrombin time, platelet count (blood count) and rapid pregnancy tests (in the case of women of childbearing age) to confirm the eligibility criteria. If the patient has underwent part or all the tests in the last 3 days, the results may be considered to verify the eligibility.

### 3.7 Contraception in the study patients

Although data from animal studies show that the studied doses had no effects on reproduction and embryotoxicity, the study will offer free condoms (male and female, depending on the participant's choice) for all men and women of childbearing age, as well as use guidance and orientation to sexual abstention for a period of 30 days from the study's inclusion.

### 3.8 Study Visits

For the HALOS trial, there will be three in person visits, one at the research center (day 1 - baseline) and two home visits (day 5 and day 10), two follow-up visits via phone call (day 14 and day 28). The study visits and their particularities are described below:

#### *3.8.1 Day 1 - baseline*

- Eligibility Check;
- Informed Consent Process and signature of the Form;
- Randomization;
- Collect demographic and baseline data;
- Collection of laboratory tests: complete blood count (CBC), urea, creatinine, alkaline phosphatase, gamma-GT, aspartate aminotransferase, alanine aminotransferase, direct and indirect

bilirubin, C-reactive protein, prothrombin time with RNI, activated partial thromboplastin time, fibrinogen, , sodium and potassium;

- Collection of nasopharyngeal swabs for SARS-CoV-2;
- Collection of urine for pregnancy test (in the case of women of childbearing age);
- Dispensing and guiding the use of study medication.

### *3.8.2 Day 5 – At home*

- Collection of nasopharyngeal swabs for SARS-CoV-2;
- Collection of blood tube for analysis of serum level of halofuginone.

### *3.8.3 Day 10 – At home*

- Collection of laboratory tests: complete blood count, urea, creatinine, alkaline phosphatase, gamma-GT, aspartate aminotransferase, alanine aminotransferase, direct and indirect bilirubin, C-reactive protein, prothrombin time with RNI, activated partial thromboplastin time, fibrinogen, , sodium and potassium.
- Collection of nasopharyngeal swabs for SARS-CoV-2;
- Collection of blood tube for analysis of serum level of halofuginone;
- Withdrawal and medication accounting from the study.

### *3.8.4 Day 14 and day 28 - follow-up via phone call*

- Telephone follow-up to collect clinical data.
- At the follow-up visit on the day 14, information on the patient's status will be requested on the ordinal symptom scale (1. not hospitalized, without limitation of daily activities; 2. not hospitalized,

with limitation of daily activities; 3. hospitalized, unnecessary of supplemental oxygen; 4. hospitalized, requiring supplemental oxygen; 5. hospitalized, requiring high-flow nasal oxygen therapy, non-invasive mechanical ventilation, or both; 6. hospitalized, requiring blood oxygenation through a membrane system (ECMO), invasive mechanical ventilation, or both; 7 Death), presence of symptoms (myalgia, fever, shortness of breath, cough, diarrhea, nausea, vomiting and headache) and presence of adverse events (bleeding or other adverse events or symptoms reported by the patient).• At the follow-up visit on the day 28, information on vital status, need for hospitalization, need for invasive mechanical ventilation (in case of hospitalization) and presence of adverse events (bleeding or other adverse events or symptoms reported by the patient) will be requested.

### 3.9 Allocation concealment and randomization

Patients will be randomized in the proportion of 1:1:1, for the control arms, halofuginone 1mg and halofuginone 0.5mg. The randomization list will be generated electronically by an independent statistician using a specific software. Randomization will be performed in blocks and will be stratified by age (<60 years and ≥ 60 years).

The allocation concealment of the randomization list will be maintained through an automated and centralized randomization system accessed via the internet, available 24 hours a day. Patients who do not meet the eligibility criteria to participate in the study should not be recruited and randomized, and this will be considered a violation of the protocol. Patients, principal investigators and local staff will be kept blind to the allocation; only the sponsor will be aware of the blinding codes. The assessors and statisticians responsible for the results will be kept blind in relation to the allocated treatments.

